#### 2.3.1. Experiment A—Triadic synchrony

Participant pairs will be seated in front of a 27-inch computer screen (*distance* = 1.5 m) and stimuli will be presented using Presentation Software (Version 23.1; Neurobehavioral Systems Inc., Berkeley, CA, USA).

##### 2.3.1.1. Picture viewing task

A block design has been chosen to avoid serial position effects for emotionally arousing and neutral pictures [(23); see Figure 1] Neutral (N), pleasant (P), and unpleasant (U) picture blocks will be presented in six orders randomly assigned to each participant pair (NPU, NUP, UPN, etc.). Pictures will be presented for 3,000 ms following a fixation cross of 500 ms (varying inter-stimulus interval 2,000, 2,500, and 3,000 ms). Individual self-paced Self-Assessment Manikin (SAM)-ratings for valence and arousal on a 9-point Likert scale (46) will follow each picture presentation.

**FIGURE 1 F1:**
[figure not shown]
Picture viewing task. Blocked presentation of unpleasant (U), neutral (N), and pleasant (P) pictures for 3000 ms, following a 500 ms fixation cross; self-paced Self-Assessment Manikin (SAM) ratings follow each picture presentation. Variable inter-stimulus interval (ISI) of 2,500, 3,000, and 3,500 ms.

##### 2.3.1.2. Imagination tasks

In the silent reading + imagination task (see Figure 2), each script will be presented for 15 s followed by a 12 s imagination period. Each imagination will be followed by a SAM-rating. A variable inter-stimulus interval of 15, 16, and 17 s will be used.

**FIGURE 2 F2:**
[figure not shown]
Imagination task. Unpleasant (U), neutral (N) and pleasant (P) scripts are presented for 15 s (listening/reading), followed by a 12 s imagination period and the self-paced Self-Assessment Manikin (SAM) rating. Variable inter-stimulus interval (ISI) of 15, 16, and 17 s.

The procedure in the listening + imagination task will be identical to silent reading, except that participants will now listen to audio files. Emotion order and reading/listening tasks will be counterbalanced between pairs. Audio files for the listening task will be read by male or female voice and will be counterbalanced, too.

#### 2.3.2. Experiment B—Dyadic synchrony

In experiment B, participants will only perform the reading/listening + imagination task, seated facing each other at a distance of 1.5 m. One partner, viewing the screen, will read out the scripts presented analogous to experiment A, the other partner (with the back to the screen) is listening. Then, both imagine the scene for 12 s and do individual SAM-ratings. After three runs (unpleasant, neutral, pleasant in counterbalanced order), positions are changed.

### 2.4. Data acquisition and pre-processing

Subjective rating data will be registered *via* Presentation Software (Version 23.1; Neurobehavioral Systems Inc., Berkeley, CA, USA) and logfiles will be further processed using IBM SPSS Statistics Version 29.0 (IBM Corp., Armonk, NY, USA) SPSS (Version 29.0, Armonk, NY, USA). ECG and EDA will be measured using EcgMove4^1^ and EdaMove4^2^ (movisens GmbH, Karlsruhe, Germany), respectively. For the continuous single channel ECG signal (sampling rate of 1024 Hz), a dry electrode chest belt associated with the EcgMove4 system will be used. An EDA sensor associated with the EdaMove4 system will be used to continuously measure EDA (sampling rate of 32 Hz) using a wrist-band and two disposable electrodes are attached to the hypothenar. The built-in activity sensor will register acceleration in three-dimension, angular rate (gyroscope), air pressure and temperature.

Raw sensor data will be read out, visualized and saved using the free and open software UnisensViewer (movisens GmbH, Karlsruhe, Germany), and will then be exported into MATLAB (The MathWorks Inc., Natick, MA, USA; raw ECG data and skin conductance level, SCL, for EDA). For subsequent analyses, ECG raw data will be digitally sampled down at 400 Hz and corrected for artifacts using the Autonomic Nervous System Laboratory [ANSLAB; (47)]. The software automatically detects R-wave-triggers to marker single heart beats; misplaced R-wave-triggers will be checked and corrected whenever they occur. The data will be converted into heart rate in beats per minute for every half-second bin of the sampling period and further analyzed with SPSS. The built-in activity sensor data (acceleration in three-dimension, angular rate, and temperature) will be analyzed together with EDA because of the potential influence of these variables on EDA. To control for possible effects of differences in the overall skin conductance level (SCL) on phasic SCL changes, SCL will be range-corrected per subject using all available data points during all experimental tasks. Both, SCL and heart rate (computed by converting RR-intervals into beats per minute) will be reduced into 1 sbins for synchrony analyses.

Electroencephalogram will be measured using two nine-channel B-Alert X-Series mobile-wireless EEG systems^3^ (BIOPAC Systems Inc., Goleta, CA, USA). Channel configuration includes F3, F4, C3, C4, P3, P4, Fz, Cz, and POz (monopolar configuration) with linked mastoids as reference. EEG data acquisition and pre-processing will be realized *via* Acq*Knowledge* Acquisition and Analysis Software (BIOPAC Systems Inc., Goleta, CA, USA; including high-pass and low-pass filtering at 0.1 Hz and 67 Hz, respectively).

### 2.5. Data analysis

Questionnaires and behavioral data will be imported from Presentation into SPSS (Version 29; IBM, Armonk, NY, USA).

To investigate the emotion effect, ANOVAs involving the within-subjects factor emotion (unpleasant vs. neutral vs. pleasant) will be conducted. Involving the additional between-subjects factor partner (partner 1 vs. partner 2), requires a total sample size of *N* = 42 to reveal medium size effects [obtained with G*Power, Version 3.1; alpha error probability = 0.05; power = 0.95; partial η^2^ = 0.06; (48)]. For theses analyses, heart rate will be extracted between 1 s prior to picture onset (baseline) and picture offset (3 s). Skin conductance change will be scored as the maximum response (between 1 and 3 s after picture onset). During the imagery reading/listening task, autonomic reactions will be determined by subtracting amplitudes in the first second prior to script presentation from response averages during the 15 s read and 12 s imagery periods.

For ERP analyses, data will be segmented starting 100 ms before (baseline) and 1.200 ms after stimulus onset for each sensor and means ERPs for each emotion category and subject are calculated [see (23)]. Time-windows and sensor sites for EPN and LPP analyses will be chosen following visual and statistical data inspection of individual averages for each valence category, using Randomization Graphical User interface toolbox (49).

For the picture viewing paradigm, each valence block is expected to last approximately 15 min, depending on the speed of the self-paced SAM-ratings. In the imagination task, a run including the three valences will take about 3.5 min, again depending on individual SAM-rating durations.

Thus, for synchrony analyses, signal streams will be synchronized for both subjects and then transformed in interval data. These time rows will be imported into SPSS for further analysis.

For this purpose, EEG data will be exported as MATLAB file (synchronized data for both individuals) and transformed *via* script into Brain Vision Analyzer (Version 2.2.2; Brain Vision, Morrisville, NC, USA) format to allow for artifact correction, filtering and further processing with dual electroencephalography (EEG) analysis pipeline [DEEP; (50)].

Moreover, correlational analyses and Actor–Partner Interdependence Models (APIM) are planned to analyze the influence of synchrony on subjective and interpersonal ratings (51, 52). Separate APIMs are planned for each measure (Heart rate, skin conductance, EEG) in the different tasks (independent variables) and subjective bonds-rating after the experiments (dependent variables).

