**Methods and design:**

Individuals (18−30 years) will participate in same-sex pairs in two experiments. In the first experiment (triadic interaction), both participants attentively watch unpleasant, neutral and pleasant pictures, and read/listen to standardized scripts (unpleasant, neutral, and pleasant, respectively) for the imagination task. In the second experiment, participants will read out three scripts (unpleasant, neutral, pleasant) to each other, followed by a joint imagination period. Stimuli will be presented in counterbalanced orders. After each picture and imagination, participants rate their subjective arousal and valence. In the beginning and in the end of the procedure, dyads rate their relationship, sympathy, and bonds (Working Alliance Inventory subscale). Heart rate, electrodermal activity and electroencephalogram will be continuously measured during both experiments using portable devices (EcgMove4 and EdaMove4, nine-channel B-Alert X-Series mobile-wireless EEG). Synchrony analyses will include the dual electroencephalography analysis pipeline, correlational analyses and Actor–Partner Interdependence Models.

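### The emotion ANOVA and its N = 42 treat the two members of a pair as independent; if partners' emotion contrasts correlate positively, the emotion test is liberal and the emotion × partner test conservative

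*Protocol article*

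**What the plan says.** Section 2.5 of the protocol article describes the emotion analysis as follows: "ANOVAs involving the within-subjects factor emotion (unpleasant vs. neutral vs. pleasant) will be conducted". It adds a second factor and takes the sample size from the resulting layout: "Involving the additional between-subjects factor partner (partner 1 vs. partner 2), requires a total sample size of" 42, from G*Power with "alpha error probability = 0.05", power 0.95 and "partial η^2^ = 0.06".

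The sampling unit is the pair. The abstract says that individuals "will participate in same-sex pairs in two experiments", section 2.3.1 seats each pair in front of one screen, and section 2.3.1.1 presents the picture blocks "in six orders randomly assigned to each participant pair". In Experiment B (section 2.3.2) one partner reads aloud while the other listens. "After three runs (unpleasant, neutral, pleasant in counterbalanced order), positions are changed", so each person takes both roles.

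Section 2.5 also plans Actor–Partner Interdependence Models, but for the relation of synchrony to the ratings. No dyad term is named for the emotion ANOVA, which serves the primary question in section 2.6.

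**The concern.** A between-subjects factor tells the ANOVA that its levels hold different, unrelated people. Here each person at level 1 has a matched person at level 2, from the same session and with the same block order. The emotion test then uses an error term with 80 degrees of freedom from 42 supposedly independent people, where the design supplies 21 independent units.

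Emotion varies within person, so partners who merely resemble each other in overall level (both with a fast heart rate, say) do no harm, because the level cancels in the contrast. What matters is whether partners' emotional-minus-neutral contrasts correlate. If they do so positively, the mean contrast is less precise than the ANOVA believes and the emotion test rejects too often. The difference between partners is then more precise than the ANOVA believes, and the emotion × partner test rejects too seldom.

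At stake are the error rate of the primary test and the power statement behind N = 42.

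**Working it through.** **Inputs from section 2.5.** Three emotion levels (m = 3), two partner levels, N = 42 persons (21 pairs), alpha 0.05, power 0.95, partial η² = 0.06.

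**Assumptions, not in the article.** Correlation between emotion levels r = 0.5; sphericity (ε = 1); and c, the within-pair correlation of the emotion contrasts.

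**Step 1: reproduce N = 42.**
- f² = 0.06 / (1 − 0.06) = 0.0638.
- λ = f² × N × m / (1 − r) = 0.0638 × 42 × 3 / 0.5 = 16.09 (f² unrounded).
- df1 = m − 1 = 2; df2 = (N − 2)(m − 1) = 40 × 2 = 80; critical F = 3.111.
- Noncentral F(2, 80) with λ = 16.09 gives power 0.951, for the emotion effect and for emotion × partner alike.

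42 is the smallest even N that reaches 0.95, so the stated figure is that of two independent groups of 21. With r = 0 the same calculation needs 84, which is why r = 0.5 is inferred.

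**Step 2: type I error of the planned tests.** With correlation c, the variance of the mean contrast is (1 + c) times its value under independence, and that of the between-partner difference is (1 − c) times. To a good approximation:
- emotion: P[F(2, 80) > 3.111 / (1 + c)]
- emotion × partner: P[F(2, 80) > 3.111 / (1 − c)]

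With 2 numerator df the tail probability is (1 + 2F/80)^(−40). For c = 0.3, for example, 3.111 / 1.3 = 2.393 and (1 + 2 × 2.393/80)^(−40) = 0.098.

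**Step 3: power of a valid test.** Testing emotion against emotion × dyad has df2 = 2 × (21 − 1) = 40, critical F = 3.232 and noncentrality 16.09 / (1 + c).

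| Assumed c | Type I, emotion | Type I, emotion × partner | λ/(1 + c) | Valid power, 21 pairs | Persons for 0.95 |
|---|---|---|---|---|---|
| −0.2 | 2.4% | 8.1% | 20.11 | 0.978 | 36 |
| 0 | 5.0% | 5.0% | 16.09 | 0.943 | 44 |
| 0.1 | 6.5% | 3.6% | 14.62 | 0.920 | 48 |
| 0.2 | 8.1% | 2.4% | 13.40 | 0.894 | 52 |
| 0.3 | 9.8% | 1.5% | 12.37 | 0.868 | 56 |
| 0.5 | 13.2% | 0.3% | 10.72 | 0.813 | 64 |

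**Step 4: simulation check.** With 21 pairs and 100,000 runs per value, the emotion test rejected in 5.0 / 6.4 / 7.9 / 9.7 / 13.2% of null data sets at c = 0 / 0.1 / 0.2 / 0.3 / 0.5. Emotion × partner rejected in 5.0 / 3.5 / 2.5 / 1.5 / 0.4%. The pair-level emotion test stayed between 4.8% and 5.1% at every c, including −0.2.

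**The case against.** The strongest reply is that the harm is conditional, and this stands. A reader might infer that the planned emotion test is anti-conservative as such. The article does not support that: the test is nominal at c = 0 and conservative below it, and no value of c is given.

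A reader might also infer that the study's own synchrony hypothesis implies a positive c. That is a different quantity. Synchrony here is coupling of two signals over time, and section 2.6.2 predicts that more synchronous pairs will give more concordant ratings. Neither says that contrasts correlate within pairs once the emotion effect common to everyone is removed. What remains is plausibility: a shared session, a block order shared within the pair, and the expected rating concordance. Against it, ratings are given individually and communication outside the interaction tasks is barred, which may keep c small.

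Three further limits also stand. The values r = 0.5 and sphericity are inferred from reproducing N = 42 and are not stated in the plan. The article does not say how partner 1 and partner 2 are assigned, so calling the label arbitrary would go beyond the text; nor need the factor be dropped. And this is a pilot that aims to replicate what section 3 treats as a well-established effect, with valid power of 0.87 to 0.94 for c from 0 to 0.3.

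None of this removes the defect. The article itself fixes the model and derives its sample size from it, so the point is not a detail left to a fuller document, and the dyadic models it does plan do not cover this test.

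**Conclusion.** The point holds as a conditional one. Declaring partner a between-subjects factor contradicts the paired design, and N = 42 is the independent-groups figure.

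If c is zero, almost nothing changes: 5% type I error and power 0.943 against 0.951. If c lies between 0.1 and 0.5, the emotion test's error rate is roughly 6.5% to 13%, the emotion × partner test's is 3.6% down to 0.3%, and valid power is 0.92 down to 0.81. The upper end rests on c = 0.5, for which the article offers no evidence. The power figures also rest on r = 0.5 and sphericity.

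Severity: should-fix. The primary test should not depend on partners responding independently when a valid version is available from the same data.

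**What to change.** Make the dyad the unit of the emotion analysis. Either keep the planned layout with partner as a within-dyad factor, or fit a mixed model with dyad and emotion × dyad terms. In both, emotion is tested against emotion × dyad, with df 2, 40 for 21 pairs in the ANOVA version.

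In Experiment B, model reader/listener role as a within-person factor, since positions are exchanged and a between-subjects partner factor cannot represent it.

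Restate the sample size as 21 pairs, with power of about 0.94 / 0.92 / 0.89 / 0.87 / 0.81 at c = 0 / 0.1 / 0.2 / 0.3 / 0.5 in place of 0.95, and label r = 0.5, sphericity and c as assumptions.

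The cost is analysis wording and a slightly less favourable power statement; no new data are needed. Only if the 0.95 target is to be kept would recruitment rise, to 44 persons at c = 0 and 64 at c = 0.5.

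### N = 42 does not give 95% power for an emotion effect of partial eta-squared 0.06 in the ANOVA-table sense; power for that effect is about 0.50

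*Protocol article*

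**What the plan says.** The sample-size statement is in Section 2.5 (Data analysis) of the protocol article. The emotion effect is to be tested by ANOVA with the "within-subjects factor emotion (unpleasant vs. neutral vs. pleasant"), and an "additional between-subjects factor partner (partner 1 vs. partner 2") is added. This model, the article says, "requires a total sample size of *N* = 42 to reveal medium size effects". The figure is described as "obtained with G*Power, Version 3.1; alpha error probability = 0.05; power = 0.95", with "partial η^2^ = 0.06".

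The article does not give the effect-size option used in G\*Power, the correlation among repeated measures, the sphericity value, or which effect in the model (emotion, partner or their interaction) was powered. It contains no other sample-size justification. Section 2.6 makes replication of the emotion effect in two-person settings part of the primary research question.

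**The concern.** For a within-subject factor, partial eta-squared is SS_effect / (SS_effect + SS_error). The error term there is what remains after stable differences between people have been removed, so the within-person correlation is already built into the number. G\*Power's default repeated-measures option works differently: it takes an effect size scaled to the spread within a condition and then applies the correlation separately. Entering a partial eta-squared of 0.06 there counts the correlation twice and makes the required sample look much smaller.

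What is at stake is how a null result is read. The Discussion (Section 3) allows that attention to emotion may be altered in dyads and offers emotion regulation as an explanation. A reader told that the study has 95% power "to reveal medium size effects" could take a non-significant emotion effect as support for that idea. If the true effect were 0.06 in the ANOVA-table sense, such a null would arise about half the time by chance.

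**Working it through.** **Inputs from Section 2.5:** N = 42, alpha 0.05, target power 0.95, partial eta-squared 0.06, m = 3 emotion levels, k = 2 partner groups.

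**Assumed, because not stated:** correlation r among the repeated measures, sphericity epsilon = 1, and independent participants.

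The test of emotion (and of emotion by partner) has df1 = m − 1 = 2 and df2 = (N − k)(m − 1) = 40 × 2 = 80. Power comes from the noncentral F distribution with noncentrality λ. The effect size is f² = 0.06/0.94 = 0.06383, so f = 0.253.

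**Step 1. Reproduce the article's figure.** G\*Power default metric: λ = f² × N × m / (1 − r). With r = 0.5, λ = 0.06383 × 42 × 3 / 0.5 = 16.09.

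| N | λ | Power |
|---|---|---|
| 40 | 15.32 | 0.940 |
| 41 | 15.70 | 0.945 |
| 42 | 16.09 | 0.951 |

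So 42 is the smallest N that reaches 0.95. The match needs f = 0.253; a rounded f = 0.25 gives 0.946 at N = 42 and requires 44.

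**Step 2. The same inputs with 0.06 as the ANOVA partial eta-squared.** Here λ = f² × df2, and r does not enter. At N = 42, λ = 0.06383 × 80 = 5.11, which gives power 0.497. N = 124 gives 0.949 and N = 126 gives 0.952, so 126 participants (63 dyads) would be needed. The remaining G\*Power convention (as in Cohen), λ = f² × N × (m − 1) = 0.06383 × 84 = 5.36, gives 0.517 at N = 42 and requires 124. Neither comes near 42.

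**Step 3. What N = 42 can detect, in the ANOVA-table metric.** Solving for the effect at df 2 and 80:

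- 95% power: partial eta-squared 0.167 (f² = 0.2005, λ = 16.04).
- 80% power: partial eta-squared 0.111 (f² = 0.125, λ = 9.99).

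These two values and the 0.497 do not depend on r.

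**Step 4. Where r does matter.** Translating the default-metric input of 0.06 into an ANOVA partial eta-squared, λ/(λ + 80), needs r, and so does the power on the default metric:

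| r | λ | Power at N = 42 | Equivalent ANOVA partial eta-squared |
|---|---|---|---|
| 0 | 8.04 | 0.70 | 0.091 |
| 0.3 | 11.49 | 0.85 | 0.126 |
| 0.5 | 16.09 | 0.95 | 0.167 |
| 0.7 | 26.81 | 0.997 | 0.251 |

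The stated 95% therefore rests on a correlation that the article does not give. If epsilon were 0.75, the required N would rise to 52 on the default metric and 154 on the ANOVA-table metric.

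**The case against.** The strongest reply is that nothing was miscalculated. N = 42 is exactly what the program returns under its default convention, and if 0.06 was meant only as a label for a conventional medium f of about 0.25 in that metric, the claim is valid at r = 0.5. This stands as far as it goes: the fault is in the effect-size metric and its label. But Section 2.5 names partial eta-squared, and for the quantity so named the design does not have the stated power.

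A second reply is that the study is a pilot, that the emotion effect is described as a common finding in individuals, and that larger effects may be well powered. That also stands. The article gives no expected effect size, so the power of about 0.50 applies only if the true effect is as small as 0.06. A third is that the option, r and epsilon are details an article may leave to a fuller plan. Their absence alone would not be a point; the mislabelled power claim is.

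Three stronger readings should be resisted:

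- Because SPSS is named (ratings are "further processed using IBM SPSS Statistics Version 29.0", and heart rate is analysed there too), a reader might infer that observed SPSS values will be set against 0.06. No section says so.
- A reader might infer that a non-significant result will be declared evidence of altered processing. The Discussion only speculates about this and sets no such rule.
- A reader might extend the criticism to the partner main effect, since partner is in the model. No hypothesis in Section 2.6 concerns a difference between partner 1 and partner 2, so its power is not at issue.

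**Conclusion.** The concern holds in this limited form. The stated 95% power belongs to an effect size in G\*Power's default metric, not to a within-subject partial eta-squared of 0.06. For the latter, power at N = 42 is 0.497 rather than 0.95, and three times as many participants (126/42 = 3) would be needed for the stated power. The effect that 42 participants can detect with 95% power is about 0.17, nearly three times the figure given (0.167/0.06 = 2.8).

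The ANOVA-table figures assume sphericity and independent participants, and they hold for any r. That the authors used the default option with r = 0.5 and epsilon = 1 is an inference from the exact match, and the equivalence of the article's 0.06 to about 0.17 depends on that r. None of this shows that the study is too small for its purpose as a pilot, or that the emotion effect will be missed.

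**What to change.** Leave N unchanged and restate the sentence in Section 2.5, for example:

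> N = 42 (21 dyads) gives 95% power for an emotion effect of partial eta-squared about 0.17 and 80% power for about 0.11 (ANOVA-table definition, assuming sphericity and independent participants; these figures do not depend on the correlation among repeated measures). Power for 0.06 is about 0.50. The sample size was derived with f = 0.253 in the G\*Power default repeated-measures metric, with a correlation of 0.5 and sphericity.

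The authors should confirm the settings in the last sentence, since they are inferred here. The Discussion or the eventual report should add that a non-significant emotion effect is not to be taken as evidence of altered processing in dyads on the ground of 95% power for medium effects.

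The cost is one less favourable stated figure. No participants, measurements or analyses change.

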The aim of the present study is to implement the measurement methodology and analysis of interpersonal synchrony using paradigms for emotion induction already established in individual settings. These allow for the simulation of emotional and neutral interactions, as they may also occur in psychotherapy, under laboratory-controlled, experimental conditions and in healthy students.

Emotions can be induced *via* various stimuli. Standardized picture material [International Affective Picture System, IAPS; e.g., (22–24)] and scripts for mental imagery [e.g., (25–29)] are particularly suitable. In contrast to neutral information, emotional content is allocated more attentional resources, and, consequently, more in-depth processing [motivated attention; (30)]. These processes can be investigated using neural (electroencephalogram; EEG) and peripheral physiological correlates, e.g., electrocardiogram (ECG, including heart rate, heart rate variability) and electrodermal activity (EDA).

During picture viewing, a triphasic pattern of heart rate response is usually observed, including (1) initial deceleration (orienting response), (2) acceleration, and (3) secondary deceleration (30, 31). The present pilot study focuses on the first two observations. Unpleasant (and, less consistently, high arousing, in contrast to low arousing pleasant) pictures have been found to evoke more pronounced initial HR deceleration, whereas pleasant pictures provoked higher acceleration relative to unpleasant [neutral pictures ranging in between; (30, 32)]. In line with these findings, evidence from appetitive and aversive conditioning suggest, that initial bradycardia might be rather valence-independent, indicating stimulus novelty or significance (33, 34).

Viewing of emotionally arousing, relative to neutral pictures has been associated with higher skin conductance level (SCL), pointing to higher sympathetic arousal (29, 30, 32). In the EEG, and especially in event-related potentials (ERPs), elevated Late Positive Potentials (LPPs) for emotionally arousing, relative to neutral pictures, have been observed over centro-parietal electrodes, starting at about 400 ms post-stimulus onset and lasting for several 100 ms, likewise indicating motivated attention (23, 24, 35). Preceding the LPP, the early posterior negativity (EPN, 150−350 ms post-stimulus onset) is also reliably enhanced for emotionally arousing, relative to neutral stimuli (36).

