### 2.6. Outcome and hypotheses

Primary research question is the successful implementation of the picture viewing and imagination paradigms from an individual setting into the two-person interaction, aiming at the replication of the enhanced attention to emotion effect [motivated attention; (30)] in subjective ratings (SAM), physiological (ECG, EDA) and neuronal (EEG) markers, and the development and testing of new data analysis strategies. Secondary outcome will be the influence of synchrony in physiological and neuronal activity during picture viewing and imagination on subjective emotion experience and interpersonal ratings after the experiment (WAI-SR).

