#### 2.6.1. Emotion effect

In line with standard ratings and previous studies, we expect higher subjective arousal ratings for emotional, relative to neutral, pictures and scenes, and valence ratings unpleasant < < *cps*:*it* > *neutral* < /*cps*:*it* > < pleasant according to the biphasic model (30). During picture viewing, we expect emotionally arousing pictures to evoke more pronounced initial HR deceleration, whereas pleasant pictures will provoke higher post-orienting acceleration relative to unpleasant stimuli over time (30). Higher skin conductance levels are expected for emotionally arousing, relative to neutral pictures (30). In ERPs, emotional modulation of the EPN is expected between 150 and 350 ms post-stimulus onset (36). Over centro-parietal electrodes, elevated Late Positive Potentials (LPPs) for emotionally arousing, relative to neutral pictures, are expected, starting at about 400 ms post-stimulus onset (23, 24, 35).

During imagery, analogous reaction patterns are expected for heart rate and skin conductance [(29, 37, 38); for summary, see Ji et al. (39)]. Possibly, the LPP emotion effect might emerge over more posterior electrodes, compared to picture viewing (40), if it is not blunted at all during imagery (41).

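### EPN and LPP windows and sensors are chosen from the same valence-specific averages that the emotion ANOVA then tests, so the stated 5% error rate does not hold for the EEG marker

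*Protocol article*

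**What the plan says.** Section 2.5 of the protocol article sets the sequence. After segmentation, "means ERPs for each emotion category and subject are calculated". Then "Time-windows and sensor sites for EPN and LPP analyses will be chosen following visual and statistical data inspection of individual averages", taken separately by valence, with a named randomisation toolbox as the tool. For the test itself, "ANOVAs involving the within-subjects factor emotion (unpleasant vs. neutral vs. pleasant) will be conducted", at an alpha of 0.05.

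Section 2.6 makes this part of the primary research question, which is to replicate the emotion effect in subjective ratings and in "physiological (ECG, EDA) and neuronal (EEG) markers".

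The article also states prior expectations. In section 2.6.1, "emotional modulation of the EPN is expected between 150 and 350 ms post-stimulus onset". The Introduction says that larger LPPs for emotional pictures "have been observed over centro-parietal electrodes, starting at about 400 ms post-stimulus onset", and section 2.6.1 repeats that region and onset as the hypothesis for picture viewing. The expectations are incomplete: the EPN has a window but no sensors, the LPP has a region and an onset but no end, and section 2.6.1 leaves the LPP region for imagery open.

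**The concern.** A window and sensor chosen because the three valence averages look or test different there will tend to show an emotion effect when the three valences are compared there, even if the differences are noise. The nominal 0.05 applies only if the choice is independent of the contrast. Section 2.5 mentions no valence-collapsed average, no independent data and no adjustment for the number of windows and sensors examined. The toolbox is named as a means of choosing them, not as the inferential test.

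Two things are at stake. The first is the error rate of the EEG part of the replication claim. The second is the effect size, which selection biases upward and which later studies building on this pilot may use for planning. The Discussion itself allows that attention to emotion may be altered in dyads and cites reduced LPP responses under emotion regulation. A weak or absent effect is therefore a real possibility, and this rule tends to hide it.

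**Working it through.** **1. The plan's own figure.** Inputs from section 2.5: partial η² = 0.06, alpha 0.05, power 0.95, three emotion levels, two partner groups. Assumed, as not stated: correlation 0.5 between repeated measures, sphericity.

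- f² = 0.06 ÷ 0.94 = 0.0638, so f = 0.2526.
- λ = f² × N × 3 ÷ (1 − 0.5) = 0.0638 × 42 × 3 ÷ 0.5 = 16.1, with 2 and 2 × (42 − 2) = 80 degrees of freedom.
- Power is 0.951 at N = 42 and 0.945 at N = 41.

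N = 42 reproduces. The sample size is not in question, but it presumes a test at a true 5%.

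**2. Search space.** Nine channels (section 2.4) and 1,200 ms after stimulus onset (section 2.5). As an illustration:

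- LPP: eight adjoining 100-ms windows from 400 to 1,200 ms over six centro-parietal sensors (C3, C4, Cz, P3, P4, POz) give 8 × 6 = 48 cells.
- EPN: four 50-ms windows from 150 to 350 ms over P3, P4 and POz give 4 × 3 = 12 cells.

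If the cells were independent, the chance of at least one significant F would be 1 − 0.95^48 = 0.915 and 1 − 0.95^12 = 0.460. EEG cells are positively correlated, which lowers these values; sliding or longer windows add candidates.

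**3. Null simulation.** There is no emotion effect. A three-level repeated-measures F is computed for 42 participants, treated as independent, and the largest F in the search is taken as the result. Noise correlations are not in the article, so they were varied. Model A uses smoothed noise (25 to 100 ms) with channel correlation 0.5 to 0.8. Model B uses exponentially decaying autocorrelation (100 to 600 ms) with channel correlation 0.5 to 0.95.

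| Selection rule | Model A | Model B |
|---|---|---|
| Window and cluster fixed in advance | about 3-5% | 4.3% to 5.6% |
| LPP, best window and centro-parietal site | about 61-92% | 32-90% |
| LPP, window searched on a fixed cluster | about 26-46% | not run |
| LPP, onset held at 400 ms, end and centro-parietal site free | not run | 16-47% |
| EPN, best cell, posterior sensors | about 16-39% | not run |
| EPN, window free within 100 to 400 ms, any site | not run | 23-82% |

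The search areas of the two models are not identical, so the columns show a range and not a like-for-like comparison.

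**4. Threshold and effect size.** The ordinary critical F (2 and 82 df) is 3.11. Under model B, the 95th percentile of the best-pick LPP F over centro-parietal sites is 5.61 to 8.21. With partial η² = 2F ÷ (2F + 82):

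- Fixed cell: 6.22 ÷ 88.22 = 0.070.
- Best pick: 11.22 ÷ 93.22 = 0.120, to 16.42 ÷ 98.42 = 0.167.

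So with no effect at all, one best-pick result in twenty would show a partial η² of at least 0.12 to 0.17, about two to three times the 0.06 used for planning.

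**5. Requiring the expected direction.** Under the null, neutral is equally likely to rank lowest, middle or highest, so a fixed cell gives 0.05 ÷ 3 = 1.7% in the predicted order. Best-cell picking gives about 9-21% or 22-56% for the LPP, depending on how the directional criterion is applied, and 6-15% for the EPN. Searching only the window on an averaged cluster gives 8-16% (LPP) and 4-8% (EPN). Inflation is smaller in absolute terms but remains.

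**The case against.** - **Best-cell picking is not what the plan says.** True. Section 2.5 speaks of windows and sites in the plural and does not say that the largest F wins. The best-cell rates are therefore worst cases and not forecasts. Milder searches still exceed 5%.
- **A reader might infer that a positive EEG replication is close to guaranteed.** The documents and the figures do not support that. For the EPN searched within its stated window over posterior sensors, even the worst case is 16-39%. For the LPP, the higher rates count any significant omnibus F, whereas section 2.6.1 predicts a direction.
- **A reader might infer that the plan already holds complete prior windows, so that data-driven choice is needless.** It does not. EPN sensors and the LPP end are missing, and for imagery the article says that the evidence is sparse and conflicting. Some tuning is understandable there, but it need not use the tested contrast.
- **The randomisation toolbox may control multiplicity.** It could, if a test corrected over all sensors and time points were itself the inference. The article uses the toolbox for choosing and states no correction either way.
- **This is a pilot, and trying out new analysis methods is one of its aims.** This stands as a reason to keep exploratory maps. It does not justify a replication test in windows drawn from the contrast under test.
- **The detail may sit in a fuller plan.** The objection is to a rule that the article states, not to an omission.

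**Conclusion.** The concern holds in a limited form. The stated rule selects on the contrast that it then tests. It therefore raises the false-positive rate above 0.05 and biases the EEG effect size upward for one of the primary replication markers. The direction is certain if the rule is followed as written, and inflation appeared in every noise setting tried.

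The size is not fixed by the documents. Under best-cell picking with channel correlation 0.5-0.8, the omnibus rate is roughly 60-90% for the LPP and 16-39% for the EPN, against about 3-5% with a pre-set window and cluster. For the areas searched these are upper bounds. Stronger channel correlation lowers the LPP figure (to 32% at the lowest setting run), requiring the predicted direction lowers both, and letting the EPN search run beyond its stated window and posterior sensors raises that figure. The sample size of 42 and the ratings, heart-rate and skin-conductance analyses are not affected.

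**What to change.** Make the change before any valence-specific average is inspected, because afterwards it cannot be credited.

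**Picture viewing**, one of:
1. Pre-set both components. EPN: mean over 150-350 ms (section 2.6.1) at named posterior sensors, for example P3, P4 and POz, a choice that the protocol must add. LPP: mean from 400 ms to a stated end within the 1,200 ms epoch, over named centro-parietal sensors.
2. Choose windows and sensors on the average collapsed across the three valences.
3. Make a randomisation test corrected over all sensors and time points the inferential test.

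**Imagery:** use option 2 or 3, or label the result exploratory, since the LPP region is left open.

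Valence-specific data-driven maps can stay, labelled exploratory.

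The cost is a few sentences in the analysis section; design, recruitment and sample size do not change. The downside is small: a pre-set window may lie slightly off the optimum in dyads and lose a little power.
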